#### Modifications

The range of possible activities of APNs is broad and flexible. A deviation from the protocol could arise if a patient wishes to be cared for by the physician instead of the APN more than actually intended, thus preventing APNs from fulfilling their potential. In this case, the primary care physician will be involved in the care as needed.

#### Adherence

The introduction of APN roles and APN care in primary care practices is new for everyone involved. Including APNs, primary care physicians and patients. The primary burden for this implementation process falls on APNs, but physicians are also involved. Therefore, pioneer APNs are supervised by experienced mentors during their role development process in primary care. This mentoring consists of weekly short phone calls and monthly structured evaluation interviews. In addition, mentors conduct quarterly structured interviews with primary care physicians. Depending on the needs that become clear in the various conversations, supportive activities by the mentors can follow, with the aim of ensuring the implementation of the planned intervention.

#### Concomitant care

Based on patient needs, other health care providers besides the APN and GPs (e.g., physiotherapists, medical specialists) might be needed, which is accepted in this study.

### Outcomes

#### Primary endpoint

The primary endpoint is the number of emergency contacts per patient within one year. Emergency contacts are visits to the on-call medical service, GP contacts outside office hours and unplanned hospital admissions.

#### Secondary endpoints

The secondary endpoints in question are the use of continuing care institutions (inpatient hospitalizations, specialist visits, and nursing home stays), hospital readmission and home visits by primary care physicians. In addition, the expectations and experiences of participating physicians, APNs, and patients are mapped, and the financial impact of the intervention will be measured. The primary and secondary endpoints will be assessed by the IMBEI.

Outcomes of the internal evaluation are the health status of the patients and the satisfaction of physicians, patients and relatives with the APN care. In addition, the role development of the APNs and the experiences of the medical assistants are evaluated.

### Participant timeline

The initial data of the participating patients includes age, sex, medical diagnoses, and number and duration of illnesses. These data are collected during the enrolment phase. Each patient enrolled in the project takes part in APN care for twelve months. The initial assessment lasts on average 1.5 hours. Follow-up contacts for the implementation and continuation of the care plan usually take place every four weeks. Depending on the need, however, the intervals can also be significantly shorter or significantly longer. APN contact is held at least quarterly. Routine contacts last on average 30 minutes. Depending on patient concerns and needs, the time frame may vary.

Routine data are used to count emergency contacts as the primary outcome measure, which means that there is no time stress for the patients. Secondary data are supplied by the ASHIP and by one health insurance company. However, there are patients for whom not all data regarding hospital and emergency contacts are available from routine data. For them, data are collected by the APNs. These data are also used for the analysis of secondary endpoints and health economic analyses. In addition, 30 patients will be interviewed about their experiences after completion of the 12-month intervention. We do not foresee the need for follow-up data collection.

The assessment tools mentioned above are used to measure the health status of the patients in the internal assessment. Data will be collected at the beginning (t0) and at the end (t1) of the 12-month intervention. Patient satisfaction with APN care is measured using a project-specific questionnaire.

The participants’ timeline in relation to the individual steps that occur during enrolment, intervention and evaluation is shown in Table 2:

**Table 2 Tab2:**
[figure not shown]
Participant timeline

### Sample size

The number of cases was calculated on the basis of the number of emergency contacts after twelve months (primary outcome). Based on literature estimates, it was assumed that the expected number of 2.7 emergency contacts per patient per year could be reduced by approximately 15% to 2.295 emergency contacts. The alpha was assumed to be 0.05. Taking into account the cluster effect and a dropout of 30% and a target power of 80%, this results in 817 patients in the intervention group and 1634 patients in the control group.

### Recruitment

Recruitment of patients will be carried out by the participating general practitioners through a direct approach. Patients trust their GPs, so a recommendation to participate made by primary care physicians is likely to result in a high participation rate. The recruitment process is supported by the offer of personal contact between APNs and potential participants in the enrolment phase. In addition, to support recruitment, the patients are provided with comprehensive information and educational material about the project in easy-to-understand language, informing them about the project, its objectives and the data collection and processing that will be carried out to achieve the project goals. Posters and flyers are placed in the waiting rooms of the participating GP offices and are customized with the individual data of the general practice and the APN.

## Methods: assignment of interventions

The study reported here is a nonrandomized and nonblinded study. This means that the issues on allocation and blinding are not applicable.

## Methods: data collection, management, analysis

### Data collection methods

For the independent evaluation, data from ASHIP and the health insurance fund will be used for primary and secondary endpoints. To fill in missing data, such as hospital visits for patients with other health insurance, APNs collect health-related data and document patients' emergency and routine visits to any health-related facility (doctor's office, hospital, emergency room). The health insurer provides a data pool for control group matching. All data are transferred to the IMBEI in pseudonymized form. Patients, GPs, and APNs are informed by mailed invitations about the possibility of interview participation and asked to complete a feedback form. Potential interviewees are called via the feedback form, and appointments are made. The qualitative interviews are conducted by telephone using a previously prepared standardized interview guide. There is a separate guide for each interview group, which is finalized after piloting. Interviews are audio recorded and transcribed verbatim.

As part of the internal evaluation, the health status of each participating patient was measured before (t0) and at the end of the patient-individual intervention phase (t1) using the assessment instruments mentioned in the intervention section above as we use the data from these instruments for care and research purposes. Their psychometric data are as follows: DemTect: interrater reliability *r* = 0.993, sensitivity 85.1%, specificity 97% [14]; MNA: internal consistency α = 0.701, test–retest reliability *r* = 0.697 [23]; NRS: with a cut-off point NRS > 4, the sensitivity of ‘unbearable pain’ is 83%, while the specificity is 96.7%, with a cut-off point NRS > 5, the sensitivity is 94%, while the specificity is 85% [24]; PDI: internal consistency α = 0.86, [17]; HAQ: internal consistency α = 0.78–0.98 [25, 26]. The psychometric results of the German translation are as follows: test–retest reliability 0.94, internal consistency α = 0.92, criterion validity 0.76 [27]; MILVA: internal consistency range between α = 0.61–0.94, sensitivity 72%, specificity 59%; [17]. PAINAD-G: internal consistency α = 0.85, interrater stability *r* = 0.80, retest reliability* r* = 0.90 [21]; DEMMI: internal consistency α = 0.83, interrater reliability ICC 0.94 [28].

For the internal evaluation of patients’ satisfaction with APN care, a standardized questionnaire is used before and at the end of the patient-individual intervention phase. We take the APN-BQ (Advanced Practice Nurse- counselling quality) questionnaire and modify it for project-specific concerns. The APN-BQ aims to measure the quality of advanced practice nurse counselling in home care settings. The APN-BQ has shown itself to be a reliable instrument with good content and construct validity. The value is α = 0.86 [29]. The questionnaire for relatives was adapted to the patient questionnaire, which made sense from a thematic point of view. The timing of the data collection runs parallel to the data collection from the patients. All GPs in the participating practices are questioned via standardized project-specific questionnaires at the beginning (t0) and the end (t1) of the project intervention. In addition, qualitative interviews are conducted with medical assistants as well as with the APNs. Two medical assistants from each participating general practice are interviewed before (t0) and at the end of the 24-month period of project intervention (t1), and all nine APNs are interviewed before (t0), after 12 (t1) and after 24 months (t2) of intervention. The interviews of both groups are guideline based.

### Data management

Data from patients in the intervention group will be entered by the APNs. For this purpose, a special secure software that stores all data securely and provides secure data transfer to the trust centre has been developed. The IMBEI receives the pseudonymised data from the trust centre as well as from the health insurance funds and the ASHIP by means of Qiata File Transfer Appliances. All data, which have already been checked and cleaned by the ASHIP and the health insurance fund, as well as the data of the APN entries, are again subjected to a quality and plausibility check by the IMBEI.

Both quantitative and qualitative data received by the IMBEI are stored in a secure network at the University Medical Center of the Johannes Gutenberg University Mainz. The appropriate technical and organizational measures according to the General Data Protection Regulation (GDPR) are listed in a separate document. Upon completion of the project, all data will be archived and secured in accordance with applicable laws.

### Statistical and further methods

#### Statistical and further methods for primary and secondary outcomes

Statistical analyses of the independent evaluation take place as a comparison between intervention and control groups. Poisson regression will be used for both the primary and secondary endpoints. Adjustments are made for relevant confounders but not for matching variables. APN practices in the intervention group are not considered clusters because a comparable cluster variable is not available for the control group.

Users of the new form of care (patients, participating primary care physicians, and APNs) will be interviewed in qualitative interviews. The interviews will take place at the end of the intervention period to reflect the experiences made. Additionally, primary care physicians will be interviewed at the beginning of the project to map expectations of the new form of care. It can be assumed that a theoretical saturation – i.e., the point at which new interviews no longer provide additional information – will be reached with *n* = 5 GPs and *n* = 5 APNs. Full data collection from all 9 practices participating in the project will nevertheless be targeted. For patients, a number of *n* = 30 participants is expected to reach theoretical saturation.

Cost analysis from the social health insurance perspective will be performed to evaluate potential savings. Costs will be compared between the intervention and the control group. Total cost analysis and cost analysis within subgroups will be carried out to identify areas with the highest costs or cost savings. These subgroups will be identified through the primary and secondary endpoints. Data for the health economic analysis will be obtained from the participating health insurance. Intangible or nonmedical costs will not be analysed since these data are not available in the insurance dataset.

In the internal evaluation, descriptive and analytical statistical methods are used. The patient’s situation at the beginning and at the end of the APN intervention and the nursing process will be described by statistical indicators such as percentual distribution, mean and standard deviation or median and quartile deviation. Depending on the kind of data and on its distribution, parametric or nonparametric statistical analyses will be conducted (e.g., variance analysis, t test, Mann-Whitney U test or Wilcoxon test).

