### Interventions

#### Intervention description

The intervention aims to integrate person-centred and evidence-based APN care for multimorbid patients in general practices in rural areas in Germany. To be eligible for participation, the general practice must confirm its willingness to change some structural and process routines to integrate APN work into its workflow. Examples include providing a treatment room and a car for home visits as well as ensuring weekly case conferences to support APN work.

The qualification profile of APNs includes a professional nursing licence, at least two years of professional experience in nursing and an academic degree at the master’s level in a nursing-related program. In addition, APNs complete 500 h of project-specific training.

Within the scope of the study, APNs take over the care of multimorbid patients. The integration of APN care for multimorbid patients in practice is a complex intervention [13]. The complexity arises for various reasons. First, multimorbidity is defined by the number of diseases without further delineation, which means that the diseases and their combinations can vary greatly from one individual to another. The varying care needs lead to individual care goals. To achieve these different goals, APNs must take on a number of possible roles depending on the needs of the patients, and their activities must be selected and implemented flexibly.

To stabilize the individual health care situation, APNs implement the care process, establish or improve a supportive network and intensify the communication between all those involved in the provision of care. Furthermore, APNs actively involve patients in the care process and specifically promote patient autonomy. Conducting the care process means developing, carrying out, monitoring and evaluating a person-centred and evidence-based care plan.

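### Poisson regression is fixed for emergency contacts and the other utilisation counts with no allowance for variance above the mean, so intervals and p-values are likely to be too optimistic

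*Protocol article*

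**What the plan says.** The primary endpoint is a count for each patient: "The primary endpoint is the number of emergency contacts per patient within one year". It is the sum of three kinds of event: "Emergency contacts are visits to the on-call medical service, GP contacts outside office hours and unplanned hospital admissions".

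The analysis model is stated in the section on statistical and further methods for primary and secondary outcomes: "Poisson regression will be used for both the primary and secondary endpoints". The abstract also names Poisson regression for the comparison of the groups. The methods section goes on to adjust for relevant confounders other than the matching variables, and it leaves practice out of the model: "APN practices in the intervention group are not considered clusters because a comparable cluster variable is not available for the control group". It mentions no dispersion parameter, robust variance, negative binomial model or check of dispersion. The section on additional analyses announces sensitivity analyses without giving their content.

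The sentence on Poisson regression can only concern the utilisation endpoints among the secondary outcomes, because the same section gives costs and interviews their own methods.

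On the patients, the intervention description says that "the diseases and their combinations can vary greatly from one individual to another". The sample size section assumes that "the expected number of 2.7 emergency contacts per patient per year could be reduced by approximately 15% to 2.295 emergency contacts" and allows for a cluster effect and 30% dropout at 80% power. It gives no variance or dispersion of the count.

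**The concern.** A Poisson model with its usual model-based standard errors assumes that, given the covariates, the variance of the count equals its mean. Two features of this endpoint work against that:

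- **Related events.** The contacts can recur, and one deterioration can lead to several of them, for example an on-call visit followed by an unplanned admission. Both are counted.
- **Differing rates.** Patients qualify through any three or more chronic diseases, so their underlying contact rates probably differ. When rates differ between patients beyond what the covariates explain, the variance of the count exceeds its mean.

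If so, the estimated rate ratio remains consistent, but its standard error is too small by the square root of the variance-to-mean ratio. The confidence interval is then too narrow and the p-value too small. The trial's main conclusion rests on this comparison, so the risk is that a chance difference is declared an effect. The same holds for the secondary utilisation counts.

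**Working it through.** **Inputs from the article.** Rates 2.7 and 2.295 per patient-year, alpha 0.05, power 80%, 1:2 matching, 30% dropout, 817 and 1,634 patients (all from the sample size and trial design sections).

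**Inputs assumed.** Two-sided testing ("The alpha was assumed to be 0.05" leaves this open), and residual variance-to-mean ratios φ of 1.5, 2 and 3, equal in both groups. The article gives no φ, so these values are illustrations.

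**1. The plan's own figure.** 2.7 × 0.85 = 2.295 and 2 × 817 = 1,634 both check. For a pure Poisson comparison on the log scale:

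n(intervention) = (1.960 + 0.842)² × [1/2.295 + 1/(2 × 2.7)] / (ln 0.85)² = 7.849 × 0.6209 / 0.02641 ≈ 185.

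With dropout this becomes 185 / 0.7 ≈ 265. The plan has 817, of whom 817 × 0.7 ≈ 572 remain after dropout. The ratio 572 / 185 ≈ 3.1 is what the cluster effect would have to supply. The article gives no intraclass correlation or design effect, so 817 can be neither confirmed nor refuted. What it does show is that the sample size allowed for variance well beyond Poisson, while the stated analysis model allows for none.

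**2. Effect on the test.** If the true variance is φ times the mean, the Poisson standard error is 1/√φ of its correct size. Under no effect, the Wald statistic then has standard deviation √φ, so

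type I error = 2 × [1 − Φ(1.96/√φ)], where Φ is the standard normal distribution function, and coverage of the nominal 95% interval = 1 − type I error.

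| φ | 1.96/√φ | Stated SE / true SE | Type I error | Coverage |
|---|---|---|---|---|
| 1 | 1.960 | 1.00 | 5.0% | 95% |
| 1.5 | 1.600 | 0.82 | 11.0% | 89% |
| 2 | 1.386 | 0.71 | 16.6% | 83% |
| 3 | 1.132 | 0.58 | 25.8% | 74% |

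Sample size does not enter this formula, so recruiting more patients would not help.

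**3. Check by simulation.** Negative binomial counts were drawn with a mean of 2.7 in both groups, 572 and 1,144 patients, and 4,000 runs per setting. The dispersion was k = (φ − 1)/2.7.

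| φ | k | Rejections, Poisson SE | Rejections, empirical variance |
|---|---|---|---|
| 1 | 0 | 4.8% | 4.9% |
| 1.5 | 0.185 | 11.4% | 5.3% |
| 2 | 0.370 | 16.7% | 5.4% |
| 3 | 0.741 | 25.5% | 5.4% |

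The simulation error near 5% is about √(0.05 × 0.95 / 4,000) = 0.3 percentage points. The formula is confirmed. A variance estimate that allows overdispersion restores about 5% and costs nothing when φ is 1.

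**The case against.** The strongest reply is that the article names a model family and is silent on the variance estimator. Robust variance and an offset are options within Poisson regression, and a condensed article may leave them to an analysis plan that is not shown here. This stands to a degree: nothing in the text rules out robust errors. But the model is stated as a choice, the next sentences say what is adjusted for and what is left out, and a reader who follows the text gets variance equal to mean. If an analysis plan already covers this, the remedy is a short addition.

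It is also true that no dispersion is documented, that confounder adjustment will absorb some heterogeneity, and that the remark on varying diseases explains why the intervention is complex and does not describe contact rates. That is why the sizes above refer to residual dispersion and are given as a range.

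Four stronger readings are tempting, and the article does not support them:

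- **The model is wrong for yes/no secondary endpoints.** The secondary endpoint section defines none as binary. Admissions, specialist visits, nursing home stays, readmissions and home visits can all be counted.
- **Dropouts will look like successes because their observation is shorter.** Outcomes come largely from routine data described as complete or available for all patients, so leaving the nurse-led care need not end outcome capture. Deaths could shorten observation, but no rate is given and a life expectancy under 12 months is an exclusion criterion.
- **The trial is too small.** With correct standard errors, 572 and 1,144 patients give power of about 98%, 94% and 81% at φ of 1.5, 2 and 3. Any further loss from clustering is a separate question.
- **The implied inflation of 3.1 measures overdispersion between patients.** The article attributes its inflation to clustering and does not quantify it.

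**Conclusion.** The point holds for the emergency-contact count and the utilisation counts among the secondary endpoints. As stated, the analysis makes no allowance for variance above the mean, and the nature of the endpoint makes such variance likely. The estimated rate ratio is not at issue; its confidence interval and p-value are. The size is a type I error of about 11% to 26% in place of 5% for residual variance-to-mean ratios from 1.5 to 3. It rests on those assumed ratios, on a two-sided test and on model-based Poisson standard errors being used. If the residual ratio proves close to 1, the harm is negligible, and so is the cost of guarding against it.

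**What to change.** In the section on statistical methods for primary and secondary outcomes, name the model for the emergency-contact count and the other utilisation counts as negative binomial regression, or as Poisson regression with robust (sandwich) variance. Add log observed person-time as an offset where a patient is observed for less than one year. State which of the two models is primary before the outcome data are seen.

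The change is to wording only and needs no new data or patients. The downside is wider intervals when the counts are overdispersed. It does not deal with the omission of practices as clusters, which needs its own answer.

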### Explanation for choice of comparators

To evaluate whether the integration of APNs in the primary care setting improves the care of multimorbid patients, a control group from German health care insurance was selected. Persons in the control group are considered to be receiving the current standard care. Therefore, a comparison between the new intervention and standard care is possible. To minimize the risk of confounding variables, participants in the intervention and control groups will be matched for the following variables: (1) age, (2) gender, (3) comorbidity and (4) living in a nursing home.

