### Trial design

The FAMOUS trial is a prospective multicentre mixed methods study. Patients with at least three chronic conditions across nine participating general practices are eligible to be treated as an intervention group by a trained APN. All patients will be treated by APNs for twelve months. Data on the period of intervention are available as data from health insurance companies or the Association of Statutory Health Insurance Physicians (ASHIP) or data collected by the APN. The intervention group will be compared with a control group of patients from German health insurance who are matched according to age, sex, comorbidity and living in a nursing home. The matching will be performed at a ratio of one FAMOUS patient to two control patients.

Qualitative interviews will take place with GPs, APNs and patients to assess factors that are difficult to capture using quantitative data. This evaluation procedure will be carried out by an independent institution (IMBEI). In addition, the intervention will be assessed in more detail in an internal evaluation from the trial sponsor using a longitudinal design.

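### Leaving the matching variables out of a Poisson model that adjusts for other confounders can leave residual confounding in the rate ratio

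*Protocol article*

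**What the plan says.** The Trial design section of the protocol article describes controls "matched according to age, sex, comorbidity and living in a nursing home", and adds: "The matching will be performed at a ratio of one FAMOUS patient to two control patients". The section on the choice of comparators lists the same four variables and gives reduction of confounding as the reason for matching. The section on statistical methods for the primary and secondary outcomes says "Poisson regression will be used for both the primary and secondary endpoints" and fixes the covariate rule: "Adjustments are made for relevant confounders but not for matching variables". It names none of the other confounders, gives no reason for the exclusion and does not mention conditioning on matched sets. On allocation the article says: "The study reported here is a nonrandomized and nonblinded study".

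**The concern.** In a cohort matched on M, arm and M are unrelated in the matched set as a whole. If the sets are intact and the model contains arm alone, leaving M out does no harm. The plan does something else: it adds further confounders C. A confounder is related to arm, and in a nonrandomized study of multimorbid patients such variables may well be related to age, comorbidity or nursing home residence too. Among patients with the same C, the arms then differ in M again. If M predicts emergency contacts, part of its effect is credited to the intervention. At stake is the primary rate ratio, planned at 0.85, and every secondary endpoint analysed under the same rule. This is a rule that the article states, not a detail it leaves to an analysis plan.

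**Working it through.** The plan gives no figure on this point to reproduce. Its only numerical anchor is the planned effect: 2.295 / 2.7 = 0.85. The check therefore uses assumed inputs, shown with a range.

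**Assumed inputs (none is in the article).** One binary matching variable M with prevalence 0.4. One binary confounder C with prevalence 0.2 if M = 0 and 0.6 if M = 1. Log-odds of enrolment = -4 + M + C. Rate = 2·exp(0.5M + 0.5C), so each variable multiplies the rate by 1.649. True rate ratio 1.00. Exact 1:2 matching on M.

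**Step 1, marginal balance.** Enrolment probabilities are 0.0180, 0.0474 and 0.1192 for M + C = 0, 1 and 2. After matching, M = 1 in 71.65% of both arms.

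**Step 2, balance within C.** The share with C = 1 is:
- M = 1: 0.790 (intervention), 0.581 (control)
- M = 0: 0.397 (intervention), 0.195 (control)

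By Bayes' rule, the share with M = 1 is:
- C = 1, intervention: 0.7165·0.790 / (0.7165·0.790 + 0.2835·0.397) = 0.834; control, in the same way, 0.883
- C = 0: 0.468 against 0.568

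The arms are balanced on M overall but not within either level of C.

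**Step 3, effect on the rate.** The average rate factor due to M is 1 + 0.649·P(M = 1):
- C = 0: 1.303 / 1.369 = 0.952
- C = 1: 1.541 / 1.573 = 0.980

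With arm and C in the model, the Poisson score equations reduce to Σ n0c·n1c·(r1c - RR·r0c) / (n0c + RR·n1c) = 0, summed over the levels c of C. Here n1 = 0.321 and 0.679, n0 = 1.057 and 0.943, r1 = 2.607 and 5.082, r0 = 2.737 and 5.186 (C = 0, then C = 1). The solution is RR = 0.973, between the two stratum ratios. With M added, RR = 1.000.

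**Step 4, range.** The same calculation for other inputs. The two figures in each cell are for positive and negative selection on C.

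| Relation of C to M and to enrolment | C only, as planned | C and M |
|---|---|---|
| Strong (prevalence gap 0.4, log-odds ±1) | 0.973 / 1.034 | 1.000 / 1.000 |
| Mild (gap 0.2, log-odds ±0.5) | 0.990 / 1.009 | 1.000 / 1.000 |
| C unrelated to M (gap 0, log-odds ±1) | 1.001 / 1.000 | 1.000 / 1.000 |

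Random simulations of the strong case agree within simulation error: 0.973 to 0.976, and 1.031 to 1.038.

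**Step 5, other assumptions.** A separate simulation used a true ratio of 0.85, a continuous confounder, a graded matching score, overdispersed counts, about 572 intervention patients and 300 runs. C only gave 0.831 with correlation 0.3, and 0.807 or 0.908 with correlation 0.5. These lie 2%, 5% and 7% from 0.85. It gave 0.848 to 0.854 when C was independent of M. Adding M gave 0.847 to 0.855 in all these cases.

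**Step 6, precision.** In that simulation, adding M to C left the empirical standard error almost unchanged (0.0526 and 0.0526; 0.0560 and 0.0553). The plain Poisson standard error was also unchanged (0.0330 and 0.0330; 0.0322 and 0.0324). Only a robust standard error fell, by about 4-7%.

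**The case against.** The strongest reply is that no bias has been shown. It needs confounders related both to arm and to the matching variables, and the article names none. That stands: a reader might infer that the primary rate ratio is biased, but the document supports only that it can be. Adjusting for C alone also improves on no adjustment. In the strong case the crude ratios are 1.102 and 0.899, against 0.973 and 1.034, so the fault lies in what remains.

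Three other stronger readings do not hold.

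- **Size against the standard error.** A reader might set 2-4% against an independent-Poisson standard error of about 0.03 and call it a whole standard error. The sample size, however, allows for clustering. With 80% power at a ratio of 0.85 and two-sided 0.05 (the article does not state sidedness), the implied standard error is 0.1625 / 2.80 = 0.058. The strong-case bias is then 0.027 / 0.058 = 0.47 to 0.033 / 0.058 = 0.57, roughly half.
- **Lost precision.** Step 6 does not support this. Exact matching already delivers nearly all of that gain.
- **Broken matched sets.** The sample size allows for "a dropout of 30" per cent, which might suggest that matching will be undone. The article does not say whether matching precedes loss, and its missing-data section assumes complete control data and complete outpatient data. If loss from the intervention arm after matching did depend on M, it could push either way. In a simulation of the strong case with a true ratio of 1.00, the C-only result moved from 0.974 to 0.951 in one direction of selection and from 1.033 to 1.006 in the other. Coarse matching is likewise conjecture, because the article gives no categories or calipers.

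The article also plans sensitivity analyses. They are unspecified and would not change the primary estimate.

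**Conclusion.** The point holds as a stated rule that can leave residual confounding, of unknown size and direction, in the adjusted rate ratio. With a true ratio of 1.00 and the binary illustration, the range is nil, about 1%, or about 2-4%, for no, mild and strong correlation between the other confounders and the matching variables. The continuous illustration shows that stronger assumptions give more. All these figures rest on assumed correlations and are not estimates for this trial. The mechanism does not depend on them: it needs only that an adjusted confounder is related to arm and to a matching variable that predicts emergency contacts. Against a planned reduction of 15%, a shift of 2-4% is modest but avoidable.

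**What to change.** Replace the sentence in the statistical methods section with one stating that the primary Poisson model includes the matching variables (age, sex, comorbidity as used for matching, nursing home residence) together with the other confounders. Conditioning on matched sets is an acceptable alternative. Apply the same rule to the secondary endpoints. The cost is one sentence and a few extra parameters in a study planned with 817 + 1634 = 2451 patients. The variables must already be held for both arms, or the matching could not be done.
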